#### Frequency of data review

The frequency of data review is as follows: 1) participant enrollment will be reviewed monthly; 2) adverse events will be reviewed as they occur; 3) stopping rules regarding statistical power implications of dropouts and missing data will be reviewed yearly.

#### Outcome analysis

All continuous variables will be examined for normality and, if not met, outliers will be investigated and rectified, and variables will be transformed to improve the distributions or non-parametric tests will be used [134]. Univariate descriptive statistics for all variables will be examined for all sample members pooled. Missing data will be examined for missingness at random and imputed using hierarchical multiple imputation methods [135–137]. Baseline outcome measures will be summarized with means and standard deviations for each treatment arm separately. Comparisons across arms will be completed using Chi-square tests (binary and categorical variables), t-tests (continuous variables), or non-parametric tests when warranted. Change from baseline will be calculated for each outcome variable at each point in time. Change at 36 months relative to 24 months also will be calculated to examine behavior maintenance.

Mixed models will test for differences in change in outcomes 24 months post-baseline between intervention and control arms by modeling a change score with control for baseline value and including community as a random effect to reflect clustering of persons within community (the level at which random assignment will occur). For dichotomous outcomes (e.g., current smoker, met whole grain recommendation), variables will be analyzed as assessed at 24 months post baseline with control for baseline value, and community as random effect. Secondary endpoints analysis will be conducted similarly to test for 12-month and 36-month change from baseline in intervention relative to control, as well as 36-month change from 24-month to test for maintenance of any observed 24-month effects. All tests will be considered significant at p < 0.05 with two-tailed tests.

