### Outcome assessment

Outcome data will be collected via online survey which will include self-measurement of height, weight, and waist circumference; a 24-h dietary recall collected via the Automated Self-Administered 24-h Dietary Assessment Tool (ASA24) [95]; and self-reported pedometer or wearable fitness tracker readings. Survey data will be collected using the Qualtrics application. All data will be coded using participant identification numbers instead of participant names. Only the Principal Investigator and the research staff will have access to the list that matches the names with the participant identification number. Data will be stored in a secure central location and access to files will be restricted to specific study staff. The contents of identifiable data files will be encrypted to secure data. SimpleStep Rechargeable Step Counters (Pedometer Express_,_ Cedar Minnesota, USA) or a wearable fitness tracker owned by the participant (e.g., Fitbit) will be used to obtain objective data on participant PA. The participant-owned fitness tracker must be comparable to the pedometer provided by the project (e.g., 3D motion sensor). Pedometers will be worn for seven days at each time point. Participants will record their daily steps and then report them to attain valid and reliable estimates of participants’ average daily PA.

LS7 score at 24-month follow-up is the primary efficacy endpoint. LS7 is a 7-item composite cardiovascular health score correlated with prevalence of cardiovascular disease events [96, 97]. Each item is classified as poor (0), intermediate (1), or ideal (2) (see Table 3). Scores for each of the seven items are summed for a total LS7 score between 0 and 14, with higher scores indicating better health.

**Table 3 Tab3:** American Heart Association’s Life’s Simple 7 components and scoring

Indicator	Poor (0)	Intermediate (1)	Ideal (2)
Smoking	current smoker	quit < 12 months ago	never smoked or quit > 12 months ago
BMI	obese (> 30)	overweight (25–29.9)	healthy weight (< 25)
Physical activity	none	some (1–149 min/week of moderate or 1–74 min/week of vigorous)	recommended amount (≥ 150 min/week of moderate or ≥ 75 min/week of vigorous)
Healthy diet indicators met • ≥ 4.5 cups/day of FV • ≥ 2 servings/week of fish • ≥ 3 servings/day of whole grains • ≤ 36 oz/week of sugar‐sweetened beverages • ≤ 1500 mg/day of sodium	0 or 1 indicators	2 or 3 indicators	4 or 5 indicators

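### The normality rule covers the primary LS7 score and leaves its analysis method open until outcome data are seen, without requiring that a fallback keep the community clustering or the baseline value

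*Protocol article*

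**What the plan says.** The Outcome assessment section states that "LS7 score at 24-month follow-up is the primary efficacy endpoint", and builds the score as an integer sum: "Scores for each of the seven items are summed for a total LS7 score between 0 and 14".

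The Outcome analysis section opens with a screening rule: "All continuous variables will be examined for normality and, if not met, outliers will be investigated and rectified". The full set of consequences of failure is: "outliers will be investigated and rectified, and variables will be transformed to improve the distributions or non-parametric tests will be used". The rule applies to all continuous variables and makes no exception for LS7. Descriptive statistics are to be looked at with all sample members pooled.

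After the sentence on baseline summaries by arm, the same paragraph adds: "Comparisons across arms will be completed using Chi-square tests (binary and categorical variables), t-tests (continuous variables), or non-parametric tests when warranted".

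The next paragraph names the outcome model for 24-month change. It is a mixed model "modeling a change score with control for baseline value and including community as a random effect to reflect clustering of persons within community", and it notes that community is the level of randomisation. The paragraph does not say how the model relates to the earlier non-parametric option.

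**The concern.** There are three difficulties with the rule as it stands.

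- **The trigger.** The mixed model makes assumptions about residuals and community effects, not about the marginal distribution of the score. A 0–14 integer score can fail a formal normality test while the model is perfectly adequate.
- **The consequences.** A failed check opens three routes: changed outliers, a transformed score, or a non-parametric test. A transformation gives up the LS7-unit effect in which the Sample size determination section is expressed (about 1 unit for Change Club members, 0.4 unit for friends and family). Standard rank tests carry neither the baseline value nor the community effect.
- **The timing.** The choice between these routes is made once outcome data are in hand. The Communities section says that assignment cannot be concealed from research staff.

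At stake is the validity of the primary p-value. Only ten communities are randomised, and an analysis that treats their residents as independent would not hold its nominal 5% level.

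**Working it through.** **Inputs (Sample size determination; Communities).** There are five communities per arm, and the test is two-sided at 5%.
- Change Club members: 70 per arm, 10% attrition per year, 57 per arm at 24 months, ICC 0.025.
- Friends and family: 560 per arm, 20% attrition per year, ICC 0.08, described as clustering both around the member and within communities.
- Community residents: 400–500 per arm, 20% attrition per year, ICC 0.025.

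**Step 1: reproduce the plan's own figures.** With m the cluster size and n the number per arm, DE = 1 + (m − 1) × ICC, effective n = n / DE, and detectable effect = (1.96 + 0.84) × √(2 / effective n).
- Members: 70 × 0.9² = 56.7, so 57; m = 57/5 = 11.4; DE = 1 + 10.4 × 0.025 = 1.26; effective n = 57/1.26 = 45.2; detectable effect 0.59 SD. The plan says 45 and 0.60.
- Friends and family: 560 × 0.8² = 358.4. The plan's 252 reproduces with the member's social circle as cluster: m = 358.4/57 = 6.29; DE = 1 + 5.29 × 0.08 = 1.423; effective n = 251.9; detectable effect 0.25 SD. With the community as cluster, m = 71.7, DE = 6.65 and effective n = 54.
- Residents: 256–320 per arm; m = 51.2–64; DE = 2.255–2.575; effective n = 113.5–124.3; detectable effect 0.372–0.355 SD. The plan says 0.36.

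The planning figures are therefore understood, and the same design effects can be used below.

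**Step 2: size of a nominal 5% test that ignores clustering.** True size = 2 × [1 − Φ(1.96 / √DE)].

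| Sample | ICC | Cluster unit | DE | 1.96/√DE | True size |
|---|---|---|---|---|---|
| Members | 0.025 | community | 1.26 | 1.746 | 8.1% |
| Residents, 400 per arm | 0.025 | community | 2.255 | 1.305 | 19.2% |
| Residents, 500 per arm | 0.025 | community | 2.575 | 1.221 | 22.2% |
| Friends and family | 0.08 | social circle | 1.423 | 1.643 | 10.0% |
| Friends and family | 0.08 | community | 6.654 | 0.760 | 44.7% |

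**Step 3: check by simulation.** With ten communities, five against five, rounded scores and 5,000 runs, the Mann–Whitney test rejected in 7.9% (m = 11), 18.3% (m = 51) and 22.4% (m = 64) of runs at ICC 0.025. It rejected in 42.9% (m = 72) at a community-level ICC of 0.08. A t-test on community means stayed at 4.9–5.4% at ICC 0.025 and 5.7% at ICC 0.08.

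**Step 4: is the trigger likely to fire on LS7?** The plan equates 0.60 SD with about 1 unit, so the SD is about 1/0.60 = 1.67. Normal scores with that SD, rounded to integers, were simulated at total sizes from about 113 to 717 (both arms at 24 months). A Shapiro–Wilk test at 5% rejected in essentially every run, while a skewness–kurtosis test rejected in about 5%. For well-behaved data, the kind of check used would by itself decide whether the primary method changes.

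**The case against.** The strongest reply is that the plan already names a clustered, baseline-adjusted mixed model for the 24-month comparison, without exception. On that reading the opening of the section is routine data screening, and the non-parametric tests belong with the chi-square and t-tests that follow the baseline summaries. Much of this stands, and it rules out several stronger readings.

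- A reader might infer that the primary test will be unclustered and will carry the error rates in Step 2. The document does not say so. It never describes the fallback tests as ignoring community, nor does it say that they replace the mixed model. The rates are conditional on both.
- A reader might apply the inflation to all three routes. Outlier editing and transformation can stay within the mixed model, where these rates do not arise.
- A reader might give friends and family an ICC of 0.025, which yields about 24%. The plan states 0.08 for that sample, so 10–45% is the range that its own figure supports.
- A reader might take "t-tests (continuous variables), or non-parametric tests when warranted" as an unclustered outcome analysis. Its position points to baseline comparisons, and the outcome model adjusts for baseline in any case.
- A reader might infer that the method is picked on arm-level results. Descriptive statistics are examined pooled, which lessens that risk. It does not remove it, because staff know the assignment.

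The normality criterion, the named transformation and the meaning of rectifying an outlier may properly sit in an analysis plan that is not shown, and their absence is not the point here. What the reply does not answer is that the rule, as stated, reaches LS7, triggers on the wrong distribution, and permits a change of method with no condition that clustering and baseline be kept. An analysis plan would have to override that statement, not merely fill it in.

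**Conclusion.** The concern holds in a conditional form. The rule leaves the primary method for LS7 open until outcome data are seen and does not protect the features that make the primary test valid. If a standard rank test ignoring community were used, its true size would be about 8% for members, 19–22% for residents, and 10–45% for friends and family. These figures assume that the ICC of the baseline-adjusted change equals the planning ICC; a smaller one lowers them. The lower friends-and-family figure also assumes that all of the correlation lies within social circles, and the upper one that it all lies at community level. This should be fixed before outcome data are analysed. It does not show that the planned mixed model is itself invalid.

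**What to change.** Amend the Outcome analysis section as follows.
- For LS7, the mixed model of change with baseline value and community random effect, on the original scale, is the primary analysis whatever the marginal distribution. Diagnostics are on residuals only.
- Any alternative is a sensitivity analysis that keeps clustering, such as a t-test on adjusted community means or an ordinal or bootstrap mixed model. A sign-flip permutation test on the five pairs would not serve: its smallest two-sided p-value is 2/2⁵ = 0.0625, so it can never fall below 0.05.
- Only verified data errors are corrected, by someone blind to arm.
- For skewed secondary outcomes, a transformation may be used, but only within the clustered, baseline-adjusted model.

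The cost is a few sentences, with no new data and no change to the sample size. The price is giving up the freedom to change the primary method later, which is the purpose of the amendment.

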#### Dissemination of project findings

Dissemination will include multiple sectors in line with the goals of the CEBEC intervention. Results will be shared with community members, extension and community organization stakeholders, policymakers, and researchers. We will provide information on results to community members through articles in lay press (e.g., newspapers), community meetings, and on the study website. We will disseminate results to organization staff and leadership through lunchtime meetings/presentations and summary sheets. We will develop materials that are tailored to policymakers (e.g., briefs using graphics to summarize key findings), and reach researchers by publishing in peer-reviewed practice-oriented journals, including open-access journals, and deliver presentations at scientific meetings. We will share study resources and data through a resource and data sharing agreement. The PI will have access to the final trial dataset; data are available for use by others via request to the PI.

## Discussion

Evidence demonstrating positive change in behaviors and health outcomes following CEBEC interventions is limited in scope but shows notable and encouraging outcomes (e.g., increased PA) [60, 63–67]. Therefore, the opportunity to collect these data prior to implementation and throughout a follow-up period, and to do so with an adequate number of comparison communities, presents a critical and innovative research opportunity with the potential to identify effective and cost-effective strategies for dissemination. Thus, the central hypothesis is that the CC, a CEBEC intervention approach, will improve health behaviors and outcomes among engaged residents and their friends and family, and that these changes can catalyze critical steps in the pathway to improving rural health equity through improved healthy eating and PA opportunities.

## Data Availability

Data sharing is not applicable to this article as no datasets have been generated or analyzed.

## Abbreviations

AARP: American Association of Retired Persons
ASA24: Automated Self-Administered 24-Hour Dietary Assessment
AUDIT: Alcohol Use Disorders Screening Test
BMI: Body Mass Index
BSQ2: Beverage and Snack Questionnaire version 2
CC: Change Club
CCM: Change Club Member
CEBEC: Civic Engagement for Built Environment Change
CFIR: Consolidated Framework Implementation Research
DSQ: NHANES Dietary Screener Questionnaire
FV: Fruit and Vegetables
HEI: Healthy Eating Index
ICC: Intra-class Correlation Coefficient
IPAQ-long: International Physical Activity Questionnaire long version
LS7: American Heart Association’s Life’s Simple 7
MET: Metabolic Equivalent of Task
NCI: National Cancer Institute
NEMS-P: Perceived Nutrition Environment Measures Survey
NES: Neighborhood Environment Scale
PA: Physical Activity
RWJF: Robert Wood Johnson Foundation
SF-36: 36-Item Short Form Survey
